#### **Key Parameters for Sample Size Calculation:**

1. Primary Outcome: A 50% reduction in T2DM incidence in the intervention group compared to the control group.

2. Power: 80% power to detect the effect.
3. Significance Level: 5% ( $\alpha = 0.05$ ).
4. Intraclass Correlation Coefficient (ICC): 0.05 to account for clustering within mosques.
5. Dropout Rate: 50% to account for potential loss to follow-up.

The sample size calculation used the following formula for cluster-randomized trials:

$$n = 2 \cdot (Z_{\alpha/2} + Z_{\beta})^2 \cdot p \cdot (1-p) \cdot DE / (p_1 - p_2)^2$$

Where:

- $Z_{\alpha/2} = 1.96$  (for a 5% significance level).
- $Z_{\beta} = 0.84$  (for 80% power).
- $p$  = overall event rate (T2DM incidence in the control group).
- $p_1$  = event rate in the control group.
- $p_2$  = event rate in the intervention group (50% reduction).
- $DE$  = design effect, calculated as  $1 + (n-1) \cdot \rho$ , where  $\rho = 0.05$  (ICC).

*Assumptions:*

- The 5-year cumulative incidence of T2DM in Bangladesh was 16.4 per 1,000 person-years [34].
- A 50% reduction in T2DM incidence in the intervention group was assumed, based on previous trials.
- The design effect (DE) was calculated as 6.1, accounting for clustering within mosques.

*Calculation:*

1. Number of Participants per Arm:
  - Based on the formula and assumptions, 412 participants per arm were required to detect a 50% reduction in T2DM incidence with 80% power and a 5% significance level.
2. Total Sample Size:
  - To account for a 50% loss to follow-up, the total sample size was increased to 824 participants (412 in the intervention group and 412 in the control group).
3. Number of Clusters:
  - Participants were recruited from eight mosques, with approximately 103 participants per mosque.

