### 4. Sample Size

Cluster sizes were assumed to be equal in sample size calculation; actual variability was minor (range 92–110).

Calculated to detect a 7% absolute reduction in diabetes incidence (control assumed 12% incidence), with 80% power, 5% significance, and design effect (ICC=0.041 from pilot data).

Final sample: 799 participants (396 intervention, 403 control) after exclusions (25 excluded due to [specify reasons: e.g., baseline diabetes, withdrawal]).

Achieved power: 82% post-hoc (given observed ICC=0.039).

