### 5. Analysis Populations

- **Intention-to-Treat (ITT):** All randomized participants analyzed per original allocation.
- **Modified ITT:** Excludes only participants with no post-baseline data (n=10).
- **Per-Protocol (PP):** Intervention group restricted to participants with  $\geq 75\%$  attendance (verified by mosque sign-in sheets).

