### 6. Handling of Missing Data

**Primary:** Complete-case analysis. Sensitivity analyses:

- **Multiple imputation (MI):** 10 imputations using chained equations (predictors: age, sex, baseline HbA1c, mosque cluster).
- **Best-case/Worst-case scenarios:** Best-case assumes dropouts had no diabetes; worst-case assumes all developed diabetes.
- **Pattern-mixture models** to test missing-not-at-random (MNAR) assumptions.

**Report:** Flow diagram with missing data by arm and reasons.

No formal adjustment for multiplicity was applied; secondary outcome results should be interpreted as exploratory.

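### The best- and worst-case rule does not bound the effect against the intervention, the imputation model omits the glucose values that define the endpoint, and per-protocol selects attenders in one arm only

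*Combined protocol and SAP*

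**What the plan says.** SAP section 6 makes complete-case analysis primary and lists three sensitivity analyses.

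- Multiple imputation: "10 imputations using chained equations (predictors: age, sex, baseline HbA1c, mosque cluster".
- Extreme scenarios: "Best-case assumes dropouts had no diabetes; worst-case assumes all developed diabetes".
- Pattern-mixture models "to test missing-not-at-random (MNAR) assumptions", with no pattern, delta or arm specified.

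SAP section 5 defines the per-protocol set by "Intervention group restricted to participants with" at least 75% attendance; no rule is given for controls. It also defines a modified ITT set: "Excludes only participants with no post-baseline data (n=10"; the ten are not split by arm.

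The protocol's definition of terms (section 11) bases diabetes on fasting or 2-hour glucose, and SAP 7.2 cites the WHO 2006 criteria. HbA1c is not part of the definition. The biochemical timetable in protocol section 11 schedules fasting glucose, 2-hour glucose and HbA1c at 0, 4 and 12 months. SAP section 10 discloses that the per-protocol and imputation analyses were added while the analysis was under way, for robustness.

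**The concern.** With complete-case analysis as primary, what can be said about missing outcomes rests on the sensitivity analyses. Three features weaken them.

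1. A worst case should ask how bad things could be for the claimed benefit. That means dropouts on the intervention with diabetes and dropouts on control without. Giving both arms the same outcome does not ask this.
2. Imputation is only as credible as missing-at-random given the listed predictors. The list has one glycaemic marker, measured once, and leaves out the two measurements that define the event.
3. The per-protocol rule keeps the better attenders of one arm and compares them with every control. If attenders would have done better anyway, the comparison favours the intervention.

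At stake is whether a reader can judge how much missing data, in which arm, would overturn the primary result.

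**Working it through.** **Inputs.** SAP section 4 gives a control incidence of 12% and a 7-point reduction, so 5% on intervention. It also states "Final sample: 799 participants (396 intervention, 403 control) after exclusions". Protocol 10.6 plans "824 participants (412 in the intervention group and 412 in the control group". The SAP gives no numerical result for its extreme scenarios, so there is no figure to reproduce. Dropout d per arm is an assumption and is shown as a range. Simple proportions are used; no p-values are given because a simple test would ignore the eight clusters.

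**Extreme scenarios, equal dropout.** Let p_C and p_I be the incidences among those observed.

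- Best case: p(1 − d) in each arm. Risk difference (1 − d)(p_C − p_I).
- Planned worst case: p(1 − d) + d in each arm. The d cancels, so the risk difference is again (1 − d)(p_C − p_I).
- Arm-opposed: control p_C(1 − d), intervention p_I(1 − d) + d.

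| d | Planned worst, control vs intervention | RR | Arm-opposed, control vs intervention | RR |
|---|---|---|---|---|
| 0 | 12.0% vs 5.0% | 0.42 | 12.0% vs 5.0% | 0.42 |
| 3% | 14.64% vs 7.85% | 0.54 | 11.64% vs 7.85% | 0.67 |
| 10% | 20.8% vs 14.5% | 0.70 | 10.8% vs 14.5% | 1.34 |

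For the 10% row: 0.12 × 0.90 + 0.10 = 0.208, 0.05 × 0.90 + 0.10 = 0.145, and 0.12 × 0.90 = 0.108.

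The arm-opposed case reverses when 0.05(1 − d) + d > 0.12(1 − d). That is d/(1 − d) > 0.07, or d > 0.07/1.07 = 6.5% per arm.

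**Using the reported counts.** Assume 412 per arm and treat all 25 exclusions as missing outcomes: 412 − 396 = 16 on intervention and 412 − 403 = 9 on control. At design rates the events are 0.05 × 396 ≈ 20 and 0.12 × 403 ≈ 48.

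- Planned worst case: (20 + 16)/412 = 8.7% vs (48 + 9)/412 = 13.8%, RR 0.63.
- Arm-opposed: 36/412 = 8.7% vs 48/412 = 11.7%, RR 0.75.
- If the ten without follow-up data lie within the 799 and split five and five, 21 and 14 are missing. Observed events still round to 20 and 48. The planned worst case is 41/412 vs 62/412, RR 0.66; the arm-opposed case is 41/412 vs 48/412, RR 0.85.

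Neither set of counts reverses the direction.

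**Imputation.** Predictors listed: age, sex, baseline HbA1c, mosque. Scheduled but not listed: baseline fasting and 2-hour glucose, and 4-month fasting glucose, 2-hour glucose and HbA1c. Arm is not listed either. Each mosque lies wholly in one arm, so mosque determines arm only if it enters as fixed indicators.

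An illustrative simulation made dropout depend on 4-month glucose, with 10% missing and true incidence 12.0%. Complete case gave 10.6%, imputation on baseline HbA1c alone 10.9%, and imputation on 4-month glucose 12.0%. That mechanism and the correlations are assumed, and the mechanism suits the fuller model, so this shows direction only.

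**Per-protocol.** Suppose no treatment effect, a share a of the intervention arm kept, and those dropped at k times the risk of those kept. Then the apparent RR is 1/(a + (1 − a)k). With a = 0.80 and k = 1.44 it is 1/1.088 = 0.92; with a = 0.60 and k = 1.89 it is 1/1.356 = 0.74. These values of a and k are assumed; the documents give no attendance data.

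**The case against.** A reader might infer that these analyses cannot test robustness at all. The documents do not support that.

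- Pattern-mixture models are in the same list and can represent missingness that differs by arm. What is missing is their specification.
- The planned worst case is not inert. At 10% equal dropout it moves the risk ratio from 0.42 to 0.70. With unequal dropout it can reverse: at 15% on intervention and 5% on control (assumed), 0.85 × 0.05 + 0.15 = 19.3% vs 0.95 × 0.12 + 0.05 = 16.4%, RR 1.17. SAP section 6 also calls for a flow diagram of missing data by arm with reasons, so unequal dropout would be visible.
- Baseline HbA1c is a relevant predictor. How much bias the omitted glucose values would leave depends on an unknown dropout mechanism.
- Controls have no monthly sessions (protocol 10.9), so the attendance rule has no control counterpart, and the late addition of the analysis is disclosed.

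A reader might also infer that the result would reverse. Applying protocol 10.6's 50% loss allowance at the design rates gives RR 0.94 under the planned worst case and 8.75 arm-opposed. But that is a planning allowance. The SAP, written after data collection, reports 799 of 824 in the final sample and ten without follow-up data. Near 3% missing there is no reversal. Nor do the documents say that all of these analyses would be presented as confirming the primary result.

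What stands is narrower: under equal dropout neither extreme scenario can change the sign, the one method that could test arm-opposed missingness is unspecified, the imputation model leaves out relevant scheduled data, and the per-protocol comparison is selected on one side.

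**Conclusion.** The concern holds as a cheap improvement to the sensitivity analyses. The sign result is algebraic, but it needs equal dropout. The sizes rest on the SAP's design rates and assumed dropout: RR 0.54 planned vs 0.67 arm-opposed at 3% missing, 0.70 vs 1.34 at 10%, with arm-opposed reversal from about 6.5% per arm.

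Actual 12-month missingness by arm is not stated. Loss between months 4 and 12 is not given, and the reason for the 25 exclusions is an unfilled template entry. Reversal is therefore possible but not predicted.

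The imputation point concerns how plausible missing-at-random is and how efficiently the scheduled data are used; its size is unknown. The per-protocol point is selection bias, probably towards benefit, of unknown size.

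**What to change.** **Extreme scenarios.** Add the two arm-opposed extremes: intervention dropouts with T2DM and control dropouts without, and the reverse. Add a tipping-point table over the number of events assigned to dropouts in each arm. State the pattern-mixture deltas and vary them by arm.

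**Imputation.** Add baseline fasting and 2-hour glucose, and 4-month fasting glucose, 2-hour glucose and HbA1c. Include arm explicitly unless mosque enters as fixed indicators. Do not add 4-month T2DM status: those participants are already events, so it says nothing about the people being imputed. For anyone with no follow-up data only the baseline additions help.

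**Per-protocol.** Label it descriptive and do not cite it as evidence of robustness. A complier-average estimate is not a ready substitute. Sermons and walks (protocol 10.9) may affect people below 75% attendance, which strains the exclusion restriction, and eight clusters give fragile inference. It should be used only with both limits stated.

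**Cost.** SAP wording and a little programming. Data collection was complete when the SAP was written, and the added variables were already on the visit schedule. The downside is that the sensitivity results will look less reassuring.

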## 7. Statistical Methods

### 7.1 Baseline Comparisons

- Baseline characteristics were summarized as means (SDs) or proportions.
- Group comparisons used independent t-tests (continuous) and chi-square tests (categorical).
- Formal hypothesis testing of baseline differences was descriptive only.

### 7.2 Primary Outcome

**Outcome:** Cumulative incidence of T2DM at 12 months, diagnosed using WHO 2006 criteria.

**Analysis:**

- Kaplan-Meier survival curves estimated cumulative incidence.
- Group comparisons were assessed via log-rank test.
- Cox proportional hazards model with shared frailty for mosque-level clustering was used.
- HRs with 95% CIs were reported.
- The assumption of proportional hazards was tested using Schoenfeld residuals.

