#### Intervention session

Twelve (12) sessions for each subject will be carried out for the next 12 months based on the following schedule-

| Serial | Visits                   | Duration           | Tasks                            |
|--------|--------------------------|--------------------|----------------------------------|
| 1      | Initial screening | 2 -3 hours  | Lab tests only            |
| 2      | Inclusion 0 weeks | 2 – 3 hours | Motivation and Counseling |
| 3      | 1 month after inclusion  | 1 hour             | Motivation and counseling        |
| 4      | At 2 months              | 1 hour             | Motivation and counseling        |
| 5      | At 3 months              | 1 hour             | Motivation and counseling        |
| 6      | At 4 months       | 3 hours     | Motivation and Lab Tests  |
| 7      | At 5 months              | 1 hour             | Motivation and counseling        |
| 8      | At 6 months              | 1 hour             | Motivation and counseling        |
| 9      | At 7 months              | 1 hour             | Motivation and counseling        |
| 10     | At 8 months              | 1 hour             | Motivation and counseling        |
| 11     | At 9 months              | 1 hour             | Motivation and counseling        |
| 12     | At 10 months             | 1 hour             | Motivation and counseling        |

|    |              |         |                           |
|----|--------------|---------|---------------------------|
| 13 | At 11 months | 1 hour  | Motivation and counseling |
| 14 | At 12 months | 3 hours | Motivation and Lab Tests  |

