### Control group

The subjects in the control group will be educated regarding general principles of a healthy lifestyle based on the religious sermon (khutbah) that benefits T2DM prevention and informed about the current evidence showing that the lifestyle intervention is effective for T2DM prevention during the “run-in” period. After the inclusion and collection of baseline data, they will visit the study site at 4 months and 12 months for the collection of anthropometric, clinical, and laboratory investigations.

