### Phase 2: Sample survey and collection of other data

Prior to initiating the survey, the study team will organize a comprehensive training program for Imams and female assistants at BADAS’s tertiary hospital (BIRDEM Hospital) in Dhaka, complemented by hands-on training sessions at the study sites. Local volunteers will be recruited and will receive standardized training covering data collection, intervention implementation, and participant monitoring. The training curriculum will include modules on diabetes prevention, lifestyle modification, and the effective use of educational materials. To ensure adherence to study protocols, volunteers will be closely supervised by the specialized research team.

A multidisciplinary team will be formed, consisting of four diabetologists, four dieticians, two health educators, one IT specialist, two eye technicians, and six phlebotomists. This team will be responsible for overseeing data collection at baseline, 4 months, and 12 months. The team will undergo an intensive weeklong training to standardize data collection procedures. Compliance with study protocols will be rigorously monitored through regular audits conducted by data safety officers, while independent evaluators, blinded to group assignments, will carry out outcome assessments to reduce bias and enhance the reliability of findings.

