## 12. Data analysis

A data safety officer will monitor the study. The primary and secondary outcomes will be analysed using the intention-to-treat approach. Differences in baseline characteristics and clinical outcomes between the two groups will be evaluated using two-sample t-tests for continuous variables and chi-square tests for categorical variables.

For the primary outcome, the cumulative incidence of T2DM will be compared between the two groups using a log-rank test with random effects for intercept to account for pre-post correlations within participants. The intervention effect will be assessed at each time point. For secondary outcomes, which will be continuous variables, repeated-measure linear mixed models will be used to assess differences between groups over time.

The incidence rate of diabetes will be calculated by dividing the number of new diabetes cases by the total person-time of follow-up, expressed per 1,000 person-years. This method will account for participants with differing lengths of follow-up, including those who drop out or are lost to follow-up. Incidence rates will be

reported as events per 1,000 person-years, along with 95% confidence intervals (CIs), to provide a measure of precision and enable comparisons between groups.

The cumulative incidence of T2DM over the 12-month follow-up period will be estimated using Kaplan-Meier survival analysis. Differences between the survival curves will be tested using the log-rank test to determine statistical significance. To quantify the intervention effect, hazard ratios (HRs) with 95% CIs will be calculated using a Cox proportional hazards regression model, which will adjust for the time to diabetes development. Participants who do not develop T2DM or are lost to follow-up will be censored at the time of their last follow-up, ensuring accurate risk estimation.

For intervention measures, chi-square tests will be used to compare event rates between the intervention and control groups. Absolute risk reduction (ARR) and relative risk reduction (RRR) will be calculated, with risk ratios used to quantify the relative difference in event rates between the two groups. Confidence intervals for ARR and RRR will be computed to estimate the precision of the findings. The number needed to treat (NNT) to prevent one case of T2DM will be determined to evaluate the practical impact of the intervention.

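### Diabetes onset is observed only at the 4- and 12-month glucose tests, yet SAP 7.2 plans continuous-time survival analysis without defining event time or visit windows

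*Combined protocol and SAP*

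**What the plan says.** SAP 7.2 defines the primary outcome as "Cumulative incidence of T2DM at 12 months, diagnosed using WHO 2006 criteria". Its analysis list states that "Kaplan-Meier survival curves estimated cumulative incidence", names a log-rank test with no clustering attached, then a Cox model with a mosque-level shared frailty, and says "The assumption of proportional hazards was tested using Schoenfeld residuals". Protocol section 12 plans the same survival methods. It adds that participants who stay free of diabetes or are lost "will be censored at the time of their last follow-up, ensuring accurate risk estimation". It also plans chi-square comparisons of event rates, with ARR, RRR, risk ratios and NNT.

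On when diabetes can be seen, the protocol is consistent. Section 11 defines diabetes by fasting or 2-hour glucose, and its table of biochemical assessments has columns for 0, 4 and 12 months only. For controls, section 10.9 says that after baseline "they will visit the study site at 4 months and 12 months for the collection of anthropometric, clinical, and laboratory investigations". In the intervention arm's session table only months 4 and 12 are marked "Motivation and Lab Tests"; the other monthly sessions are counselling. The monitoring listed in section 10.9 covers diet, activity, blood pressure and anthropometry, not glucose.

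On who does the assessments, section 11 (Phase 2) describes a multidisciplinary team: "This team will be responsible for overseeing data collection at baseline, 4 months, and 12 months". Section 10.1 places follow-up at or near each mosque.

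**The concern.** The planned methods need a time for each event, and the trial never observes one. A case found at 12 months could have begun on any day after the 4-month test. The plan does not say whether event time is the visit date, the scheduled month or something else, sets no visit window, and mentions no grouped-time or interval-censored method.

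This matters more here than in an individually randomized trial. Testing takes place mosque by mosque, and mosque is the unit of randomization. If time from enrolment to test differs between mosques, a log-rank or Cox analysis on actual dates compares testing schedules as well as disease. With four mosques per arm, such differences need not balance. The primary test, the hazard ratio and the Kaplan-Meier curves are exposed.

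There is a second, smaller problem. Only the intervention arm has monthly contacts, so in that arm the last follow-up may be a session with no glucose test.

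**Working it through.** The plan gives no figure on this point to reproduce. The inputs are 8 mosques of about 100 (SAP section 4: 799 participants), control incidence 12% (SAP section 4) and tests at 4 and 12 months. The visit offsets are assumptions, because the documents give no visit dates or windows.

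**1. How an offset acts.** Take 400 per arm, the same 12% risk in both arms, and constant hazard: risk by week w = 1 − 0.88^(w/52). Test controls at weeks 17.33 and 52, and the intervention arm one week later. The expected log-rank table, using visit dates, is:

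| Week | Cases found | At risk I / C | Expected in I | Obs − exp in I | Variance |
|---|---|---|---|---|---|
| 17.33 | 16.7 (C) | 400 / 400 | 8.3 | −8.3 | 4.1 |
| 18.33 | 17.6 (I) | 400 / 383.3 | 9.0 | +8.6 | 4.3 |
| 52 | 31.3 (C) | 382.4 / 383.3 | 15.6 | −15.6 | 7.5 |
| 53 | 31.2 (I) | 382.4 / 0 | 31.2 | 0 | 0 |

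The 4-month visits nearly cancel. The 12-month visits do not: disease-free controls are censored at week 52, so the intervention cases found at week 53 have no comparators and count for nothing. The sum is −15.4 with variance 15.9, so Z = −15.4/√15.9 ≈ −3.85. The Cox estimate solves observed = expected and gives HR ≈ 0.36, although there is no effect. Simulation of this case (1,500 trials) agrees: 97% rejection, median HR about 0.36. By visit number, rejection is 6%.

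**2. Random mosque offsets, no effect, nominal 5%.** No between-mosque variation in risk and no dropout are assumed. The log-rank runs used 1,500 trials per scenario.

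| Assumed timing | Log-rank on dates | By visit number |
|---|---|---|
| Identical at all mosques | 5% | 5% |
| Mosque offset 0–4 weeks | 42% | 5% |
| Same, plus individual spread 0–2 weeks | 37.5% | 5% |
| Same, plus individual spread 0–4 weeks | 26% | 5% |

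An interval-censored exponential model on the same data (600 trials) rejected 4% to 6%. Cox without frailty, with mosque offsets of ±7 to ±21 days and tight batches, rejected 42% to 47%. With mosque offsets of ±7 days and individual spread of ±14 days, Cox without frailty rejected 14%; a check of the log-rank test in that setting gave 16%.

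**3. The planned frailty model, no effect.** This was fitted by penalised likelihood with gamma frailty (300–500 trials per scenario) and with log-normal frailty (300, so about ±3 points).

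- Mosque offsets of ±7 to ±21 days, tight batches: 9% to 13%. With gamma frailty, 95% of hazard ratios lay between about 0.25 and 3.8.
- Mosque offsets of ±7 or ±14 days with individual spread of ±14 days: 7%.
- Intervention mosques 4 to 14 days earlier: about 99%, median HR 3.6 to 3.7. Frailty gives no protection.
- Scheduled visit times: about 4%.

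**4. Power.** With a true HR of 0.40 and random offsets of ±14 days, the frailty model had 34% power, against 92% on scheduled times. For 12% against 5% (12% minus the 7-point reduction in SAP section 4) with mosque offsets of 0–4 weeks, the log-rank test had 74% on dates and 96% by visit number. Clustering of risk is ignored in all of these, so they show the loss from timing, not the trial's real power.

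**5. Censoring.** A control lost after the 4-month test is censored at 4 months. An intervention participant last seen at the month-11 session could be censored at 11, which adds 11 − 4 = 7 months counted as event-free without a glucose test.

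**6. Proportional hazards.** On scheduled times there are only two event times, so Schoenfeld residuals can show little more than whether the effect differs between 0–4 and 4–12 months.

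**The case against.** The strongest reply is that the harm depends on an unstated choice. Every schedule in the protocol is in nominal months, and the censoring rule is compatible with coding events at month 4 or 12. Coded that way, the tied log-rank test keeps its size. That is correct, and it is why the point is conditional.

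Staggered calendar dates are also not enough. What counts is time from enrolment to test; mosques enrolled and revisited in the same order would have little or no offset. The staffing (19 in the assessment team, plus 16 field officers and 20 volunteers in section 16) might allow sites to run in parallel. This stands too. No passage gives a visit calendar.

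Third, the planned Cox model has a frailty term, so the 42% to 47% found without it does not describe that model. Accepted: the relevant figures for random offsets are 7% to 13%. The higher range applies to the log-rank test, to which SAP 7.2 attaches no clustering. Section 12's general statement about mixed-effects adjustment does not say how a log-rank test would be adjusted.

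Finally, the chi-square comparison, ARR, RRR and risk ratio in section 12 use no dates and are not affected. NNT is affected only if it is taken from Kaplan-Meier.

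What remains is that the plan leaves the choice open, and one ordinary reading of its methods is sensitive to visit timing.

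**Conclusion.** The point holds as a gap in the primary analysis that should be closed. Onset is interval-censored between two visits, and the planned methods treat it as exactly timed without saying how time is assigned. If actual dates are used and mosques differ by one to three weeks in time to test, the log-rank test's 5% error becomes roughly 25% to 47%, falling to about 16% where individual scatter is twice the mosque offset. The frailty Cox model's error becomes about 7% to 13%, with hazard ratios too wide to be useful. These sizes rest on assumed offsets, equal mosques of 100, 12% incidence and no dropout.

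A reader might infer that detection dates were in fact used, that visit timing did differ by arm, or that the hazard ratio is therefore wrong. The documents support none of these. The large distortions under a systematic arm offset show what frailty cannot repair; nothing indicates that such an offset occurred. Nor can one conclude that Kaplan-Meier misses cases found after day 365, since no section says the curve is read at that day.

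**What to change.** In SAP 7.2:

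- Assign each event and each censoring to the scheduled visit (4 or 12 months), and state the visit windows.
- Censor at the last glucose test, not the last contact, in both arms.
- Make the primary analysis either a complementary log-log model with two intervals, log(−log(1 − h)) = interval term + β × arm, with mosque clustering, where exp(β) is a hazard ratio; or the 12-month risk compared with mosque clustering. Either needs a small-cluster correction for eight mosques.
- Use scheduled times for any Kaplan-Meier plot or log-rank test, and do not rely on the Schoenfeld test with two time points.
- State that ARR and NNT come from the 12-month risks, so that they do not depend on dates.

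The cost is SAP wording and a re-run in the software already named, on existing data. Since the SAP was written after data collection, the change should be dated and declared. If scheduled times were already used, one sentence saying so settles the timing question; the censoring rule and the log-rank test's clustering would still need stating.
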